### 2.3. Blinding

#### 2.3.1. Blinding

To minimize bias and ensure the study’s integrity, participants and researchers will be blinded to the treatment assignments. Blinding will be achieved through the use of a purpose-built sham TMS coil equipped with a magnetic shield that attenuates the TMS effects. Additionally, surface electrodes will be added to stimulate the skin during a TMS pulse, producing somatosensory effects in the skin and peripheral nerves similar to those from an intervention. This combination ensures that participants cannot discern whether they are receiving active or sham treatment based on sensory feedback. All individuals involved in the study—including participants, healthcare providers, assessment researchers, and data analysts—will remain blinded to the treatment allocations throughout the study to reduce potential biases. Each participant will receive a unique code, to facilitate data analysis without revealing information about the treatment groups. This method helps to maintain objectivity in the evaluation outcomes. The executing technician tasked with setting up the treatment will be aware of the specifics but will not engage with other participants, including the healthcare provider or the study participants.

A third person who will serve as clinical sub-investigator will be responsible for participants’ enrollment and conduction of follow-up visits complying with the criteria of Good Clinical Practices and Human Subjects Research. Each center will require some clinical sub-investigators who will receive relevant protocol information and complete training. In case of minor adverse events, these can be discussed with the principal investigators without the need for unblinding. Participants will be unblinded 6 months after the end of the study. This delayed unblinding ensures that the primary data collection and analysis phases are free from bias while still providing participants with information about their treatment allocation once the study objectives have been met. By implementing these rigorous blinding procedures, the study aims to ensure an objective assessment of treatment effects, enhance the reliability of the findings, and uphold the highest standards.

#### 2.3.2. Emergency Unblinding

Patients must be unblinded to provide the best possible care if serious neurological or psychiatric side effects or adverse events such as sudden and significant changes in mood, thinking, or neurological function occur after the rTMS procedure. These include seizures or neurological deficits, an increase in severity of depression (marked by changes in the HDRS ≥ 25), and manic symptoms like psychotic symptoms. Further changing warning signs of suicidal ideation, based on the nomenclature from the National Institute of Mental Health, like talking about the want to die or feeling unbearable pain [23], will lead us to assess the suicidal ideation attribution with the SIDAS score [24]. In case of a score ≥21, this will also lead to unblinding.

#### 2.3.3. Blinding Assessment

The providers, participants, research assessors, and data analysts’ blinding will be assessed after 3 weeks and, ultimately, after 6 weeks of treatment analyzed with Bang’s blinding index [25].

### 2.4. Participants Eligibility Criteria

#### 2.4.1. Inclusion Criteria

Adults between 18 and 65 years old;Current obsessive–compulsive disorder, as diagnosed by current DSM5 criteria by a licensed psychiatrist;Moderate to Severe OCD score on the Y-BOCS of ≥16 as a clinically significant cut-off [26];Stable maintenance treatment for at least 12 weeks;Limited response (reduction inferior to 25% at YBOCS) to previous treatment defined as patients on maintenance treatment either with cognitive-behavioral therapy and/or SSRI and previous failure to respond to at least one SSRI [6].

#### 2.4.2. Exclusion Criteria

History of stroke, seizures, epilepsy, or head injury;The presence of implanted ferromagnetic or magnetic-sensitive devices in the head or neck;Pregnant or lactating women;Previous treatment with electroconvulsive therapy;Current or previous treatment with rTMS;Presence, history or diagnosis of psychosis, substance abuse, suicide attempt, bipolar disorder, ADHD, or schizophrenia, severe major depression disorder (HDRS ≥ 25);Patients with any type of cardiac arrhythmia and cardiac devices.

### 2.5. Recruitment Strategy

Subjects are enrolled in the study at each center based on the abovementioned inclusion and exclusion criteria. Patients seen in the inpatient and outpatient settings will be consecutively recruited in the study. Furthermore, we will contact psychiatrists and psychologists through regular mail and use advertisements on social media to recruit additional patients. The recruitment process will continue until the target population (55 participants per group; see “Sample size” section) is reached. The recruitment period will extend over 6 months. A team of research assistants will be responsible for responding to any inquiries about participation via phone and email. The team of researchers will conduct the recruitment interviews through videoconferencing or in-person meetings on their sites, ensuring the IRB guidelines will be followed.

### 2.6. Adherence

To maintain adherence during the intervention, we will send weekly weekend reminders via messaging apps for the week ahead. We will ensure appointments are at similar, convenient times for each subject and at an accessible local site. If necessary, we will offer to liaise with the subject’s carers. All participants will receive a 200 USD incentive, and vouchers for transport (e.g., parking) and food will also be provided. A log of subject attendance will be used to monitor adherence [27].

### 2.7. Interventions

#### 2.7.1. Interventions

Eligible patients will be randomized equally to either low-frequency transcranial magnetic stimulation of the right dlPFC or sham. TMS is a neuromodulation technique in which a stimulator sends electromagnetic pulses to the patient’s scalp through a coil. We will use a MagVenture MagPro X100 stimulator with two dynamically cooled butterfly B70 coils: real and sham (MagVenture, Farum, Denmark).

This trial will execute an inhibitory modulation of the target area using a low-frequency protocol, defined as a pulse rate of 1 Hz. The intensity refers to the power of the pulse and is determined based on the motor threshold (MT) explained later. Lastly, the number of pulses per session will determine the duration of the session [28].

Measuring MT for each patient is required to set the adequate stimulation intensity before the TMS sessions. It will be measured for each patient once, regardless of the randomized group. The method for calculating the MT will consist of using the thumb-movement visualization. First, the primary motor cortex of the hand (M1 hand) is localized by using the C1/C2 position of the 10–20 EEG system [29]. Single pulses are applied to the M1 hand with an interpulse interval (IPI) of at least 7 s to prevent additive neuromodulatory effects. The stimulation intensity is sequentially reduced until we reach a point when fewer than 50% of the pulses lead to a muscle contraction of the contralateral hand (identified by visual inspection or neurophysiological motor-evoked potentials). The first TMS intensity that cannot elicit a muscle contraction of more than 3 out of 6 pulses is considered the motor threshold, which is the percentage of the maximum stimulator output.

Identifying the localization of stimulation to inhibit the dlPFC in each patient is critical for the efficacy of TMS. Previous trials have used the 5 cm rule to localize the stimulation site by evoking contralateral thumb movement using TMS in the motor cortex. In this way, the stimulation site is determined as 5 cm anterior to and in a parasagittal line from the point of the maximum stimulation of the motor cortex [30]. Nonetheless, this approach has been inaccurate, considering systematic variability in anatomic landmarks between patients [31]. Neuronavigation technology offers more precise and accurate TMS coil positioning than the rule of 5 method [32]. Using real-time MRI imaging, we will use the Brainsight Neuronavigation system (https://brainbox-neuro.com/products/brainsight-tms-navigation, accessed on 16 December 2023) to localize the adequate coil position.

We then will use an inhibitory protocol of 1 Hz stimulation at 100% of the MT consisting of four trains of 500 pulses, each with a 40 s inter-train interval, allowing the coil to cool. It will be a total of 2000 pulses per session with a duration of 36 min, based on the parameters by Elbeh et al. [33]. This protocol complies with published safety guidelines [28]. Sessions will occur daily, Monday through Friday, over six consecutive weeks. Sham TMS will consist of the same procedure but using the sham coil. The sham coil will be positioned in the stimulation site of dlPFC using the neuronavigation system. It will also produce similar non-specific auditory and somatosensory effects but will be equipped with a magnetic shield that attenuates the magnetic field.

#### 2.7.2. Modification/Discontinuation

Transcranial magnetic stimulation is generally safe and produces minor adverse effects or, rarely, more severe adverse effects such as seizures. The intervention protocol will follow the recommendations of the Updated Expert Safety Guidelines for TMS [34]. Adequate measures will be taken to guarantee the safety of every patient in the trial.

##### Seizures

Inducing seizures is considered a severe adverse event, but the risk associated with conventional rTMS is low, with an estimated standardized risk of 8/100,000 sessions [28]. The proposed parameters for the rTMS protocol are below the minimal parameters for seizure induction. Additionally, we will exclude patients with an increased threshold of seizures as specified in the exclusion criteria. In the event of a seizure, the rTMS will stop immediately, and the patient will be stabilized with appropriate anticonvulsants and then transferred to the nearest specialized unit for further evaluation. After a thorough investigation, the event will be reported to the Principal Investigator, the Study Safety Board, and the Institutional Review Board.

##### Hearing Loss

There is a risk of transient increases in auditory thresholds, decreasing hearing sensation. Patients with previous auditory conditions, such as individuals with cochlear implants, will be excluded from the trial. Everyone should use appropriate hearing protection, such as earplugs, during the intervention session. Any patient complaining of hearing loss, tinnitus, or aural fullness will be referred for auditory evaluation.

##### Other Minor Adverse Events

rTMS may produce minor side effects such as muscle twitching and headaches. Patients will be warned about these transient and mild symptoms before each session. Headaches usually happen after the intervention and are associated with prolonged and fixed head positioning. Patients will receive over-the-counter analgesics in the case of headaches.

### 2.8. Outcomes

#### 2.8.1. Primary Outcome Measures

Our study’s primary outcome will be comparing the groups’ Y-BOCS scores. The Y-BOCS is a validated 10-item scale, rated by trained clinicians, that evaluates the severity of symptoms in patients with OCD. Each item is rated from 0 (less severe) to 4 (more severe), with a total score of 40 [35]. Patients will be evaluated with the Y-BOCS at baseline, two, four, and six weeks of the intervention.

#### 2.8.2. Secondary Outcome Measures

Secondary outcomes include the difference in response rate and the time-to-response between the groups. The response rate will be measured as a dichotomous variable to quantify the patients who achieve clinically significant improvements. A complete and partial response rate will be defined as a reduction of ≥35% in the Y-BOCS score [36]. The latter will be defined as the time at which a partial response of a reduction of ≥25% in the Y-BOCS score will be seen.

In addition, the Clinical Global Impression (CGI) scale will be used by an experienced psychiatrist to measure the global judgment of improvement or worsening. During the assessment of the CGI scales, the psychiatrist will judge the illness severity, the patient’s level of distress, and the impact on daily functioning [37]. Moreover, the Sheehan Disability Scale (SDS) will measure the degree of disability of the patient. The SDS is a three-item self-rate scale that provides insights into the level of impairment in work, social, and family functioning [38]. We will also measure self-reported improvement in symptoms of obsessions and compulsions utilizing the Padua Inventory (PI) [39]. Lastly, patients with OCD often have depression, which could be a significant moderator of the efficacy of TMS in these patients [40]. We will measure the depressive symptoms using the widely validated Hamilton Depression Rating Scale (HDRS). The HDRS 17-item clinician-administered tool is used to measure depressive symptoms [41]. All scales will be evaluated at baseline in two, four, and six weeks.

OCD patients display abnormal regional homogeneity (ReHo) in functional MRI (fMRI) in the right dlPFC region [42]. Therefore, an additional fMRI will be conducted during the baseline MRI to localize the right dlPFC. After 6 weeks of treatment, we will assess the post-treatment fMRI.

### 2.9. Data Management

#### 2.9.1. Data Monitoring

An independent Data Monitoring Committee (DMC) of external experts in the area, without conflict of interest relevant to this study, will be established. The DMC will assess the progress, safety data and, if needed, critical efficacy endpoints. Confidentiality will be maintained during data monitoring, review, and deliberations. The Project Officer (PO) and the DMC will develop meeting agendas. Voting and minutes will be kept confidential. Open Session and Close Section reports will be prepared, presented, and appropriately distributed. Recommendations on the trial’s continuity, pause, or termination and necessary adjustments will be tracked to ensure prompt and effective implementation.

All data will be entered electronically in the trial. The original study forms will be entered and kept on file at the participating sites. The Clinical Data Management System (CDMS) will handle the data. At every visit, an electronic version of the Case Report Form (e-CRF) will be applied to all participants. The collected data from the participating sites will be sent to the Core Coordinating Center.

The entries of the e-CRFs will be monitored by the Clinical Research Associate (CRA) for completeness, and filled-up CRFs will be retrieved and handed over to the Clinical Data Management (CDM) team. The CDM team will track the retrieved CRFs and maintain their record. An Edit Check Program will be developed to detect discrepancies after validation with dummy data. In the case of data discrepancy, a Data Clarification Form (DCF) will be generated and delivered to the responsible investigator, who will have 48 h to resolve the issue. To enforce the data integrity, the CDM team will review all discrepancies regularly to ensure they have been resolved. There will be a discrepancy database where all discrepancies will be recorded and stored with an audit trail.

The study data will have restricted access. Each participating site will only be able to access its own data. The access password will be renewed regularly. All reports prepared by the Data Coordinating Center (DCC) will be prepared so that no individual subject can be identified. A complete backup of the primary DCC database will be performed once every two weeks. Incremental data back-ups will be performed daily. Errors identified by the system will be summarized and communicated to Data Managers for verification and correction. De-identified data will be made available upon reasonable request, subject to all applicable privacy laws and regulations. These tapes will be kept off-site until the study is completed. Participant files are to be stored in numerical order and will be maintained in storage for 3 years after completion of the study. Upon completion of the study, the data will be archived on secure servers for at least 15 years, as required by regulatory guidelines. De-identified data can be shared upon request, ensuring compliance with relevant data privacy regulations.

#### 2.9.2. Interim Analysis

During the interim analysis for adverse effects at 3 weeks, a Data and Safety Monitoring Board (DSMB) will ensure patient safety and determine the continuation of the trial. The DSMB will compare the rate of adverse effects, especially serious events like seizures, between the groups. Because there will be no interim statistical analysis, there is no need for alpha spending function adjustments.

### 2.10. Sample Size Calculation

Due to the study design, the primary outcome will be evaluated by a two-sided *t*-test after 6 weeks of treatment. Values from Jahanbakhsh et al. [43] were used for sample calculations, namely Y-BOCS values of 27.40 ± 4.91 (control) and 27.53 ± 4.61 (treatment) at baseline and 27.33 ± 4.15 (control) and 24.07 ± 4.35 (treatment) post-treatment. Performing the sample size calculation (STATA BE 17.0) with an alpha of 0.05 and a power of 0.9, to reduce the type II error, estimated a size of 76 participants. Due to the low adverse events in rTMS, it has a low dropout rate, from 5.3% in active use to 11.28% in sham use [44]. Additionally, the OCD patient cohort has a various dropout rate, from 17.29% in pharmacological trials, over 20.63% in active control like metacognitive therapy, to 23.49% in pill placebo [45]. Considering these two, we aim for a 30% dropout rate to ensure we do not lose power during the trial. Thus, our calculation leads to 110 participants overall, with a sample size of 55 participants per group.

### 2.11. Statistical Analysis for Primary and Secondary Outcomes

Baseline characteristics will be presented as frequencies with percentages for categorical data, or means ± SD for data with normal distribution, respectively, and medians with interquartile range (IQR) for data with non-normal distribution. Statistical analyses will be evaluated as intention-to-treat. The primary endpoint of Y-BOCS as an ordinal variable on a 40-point Likert scale will be analyzed using a *t*-test [46] and Mann–Whitney-U test, respectively, and will be adjusted to sex, depression, and baseline severity of OCD with multiple regression. Normality will be assessed using the QQ-Plot and Kolmogorov–Smirnov test.

Secondary endpoints of response rate measured by Y-BOCS will be assessed in percentages, and significance will be calculated using Fisher’s exact test. Time-to-response analysis will be conducted using the Kaplan–Meier probability.

Overall Sheehan Disability score and Hamilton Depression Rating Scale (HDRS) will be tested. 55-point Likert scales will also be analyzed using a *t*-test, respectively Mann-Whithney-U in case of non-normality distribution. The Sheehan Disability score will be compared for the three individual scores (work, social life, family life) and multiple comparison corrections via the Benjamini Yekutieli procedure. The Mann-Whitney-U test will analyze Clinical Global Impression Scales on a 7-point. Finally, the fMRI study will use the Amplitude of Low-Frequency Fluctuations (ALFF) and regional homogeneity (ReHo) analysis [47] to determine differences in the function of the brain after rTMS.

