## Abstract

Obsessive–Compulsive Disorder (OCD) is a chronic psychiatric condition with a lifetime prevalence of 2–3%. It significantly burdens quality of life and is associated with substantial economic and disease burdens. Cognitive-behavioral therapy and high-dose selective serotonin reuptake inhibitors are considered the first-line treatments for OCD. Approximately two-thirds of patients with Obsessive–Compulsive Disorder (OCD) exhibit inadequate responses to current standard therapies, thus lacking adequate therapy, resulting in a loss of quality of life and huge economic burdens. Repetitive transcranial stimulation (rTMS) is a non-invasive, safe, and well-tolerated intervention that modulates prefrontal cortical circuits involved in OCD. A previous systematic review explored the therapeutic effects of rTMS applied to the dorsolateral prefrontal cortex (dlPFC) area in patients with treatment-resistant OCD. It showed that the application of high-frequency and low-frequency (LF) rTMS to the dlPFC region yielded controversial post-treatment Y-BOCS (Yale-Brown Obsessive–Compulsive Scale) findings due to factors such as small sample sizes, short-term study durations, and variations in rTMS protocols. Objectives: Thus, we propose a theoretical protocol based on previous findings to assess better the effect of LF rTMS for treatment-resistant OCD patients. Methods: We will recruit patients with moderate to severe OCD and limited response to previous treatments from in- and outpatient clinics. We will use fMRI for precious localization of the right dlPFC and application of 1 Hz stimulation of in total 2000 pulses with three times 40 s inter-train intervals 5 days a week, in 6 consecutive weeks. The primary outcome will be the mean reduction in Y-BOCS at the end of this study. Conclusions: This study highlights rTMS’s potential to reform OCD treatment, accentuate safety, accessibility, clinical integration, and future research foundations.

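### Section 2.10 sizes the trial on an unadjusted week-6 t-test, but 2.11, 2.8.1 and the abstract do not keep it as the one deciding analysis, so the stated alpha and power need not apply to the deciding test

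*Protocol article*

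**What the plan says.** Four places in the protocol article describe the primary endpoint or its test.

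- **Abstract:** "The primary outcome will be the mean reduction in Y-BOCS at the end of this study". This is a change from baseline. The hypothesis at the end of the Introduction also speaks of a reduction over 6 weeks.
- **Section 2.8.1:** the "primary outcome will be comparing the groups" on Y-BOCS scores. Assessments at baseline and weeks 2, 4 and 6 follow. None is designated as primary, and score or change is not specified.
- **Section 2.10:** "the primary outcome will be evaluated by a two-sided *t*-test after 6 weeks of treatment". The values used are "27.33 ± 4.15 (control) and 24.07 ± 4.35 (treatment) post-treatment", and the result is stated "with an alpha of 0.05 and a power of 0.9, to reduce the type II error, estimated a size of 76 participants". Allowing for 30% dropout, this becomes 110, or 55 per group.
- **Section 2.11:** the endpoint goes to a t-test and a Mann–Whitney test, "respectively, and will be adjusted to sex, depression, and baseline severity of OCD with multiple regression". On the choice between the first two: "Normality will be assessed using the QQ-Plot and Kolmogorov–Smirnov test". No criterion for switching is given, and the regression is not labelled primary or supportive.

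**The concern.** A confirmatory trial needs one variable, one time point and one test whose result decides. Section 2.10 supplies that, but 2.11 adds a second form of analysis on equal footing, and the abstract describes a different variable. If the t-test and the regression disagree at the 5% level, the document does not say which prevails.

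Two things are at stake. If more than one result could be claimed as the primary one, the false-positive rate exceeds 5%. And the stated 90% power was computed for one candidate only; the others have different power at the same N, in one case clearly lower.

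Two smaller points belong here. The normality check moves the question from a difference in means to a comparison of ranks after the outcome data are seen. And depression as a covariate carries no time point, although section 2.8.2 measures HDRS at baseline and again at weeks 2, 4 and 6; adjusting for a post-baseline value could remove part of the treatment effect.

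**Working it through.** **Inputs from section 2.10.** Baseline Y-BOCS 27.40 (SD 4.91) control and 27.53 (SD 4.61) treatment; post-treatment 27.33 (SD 4.15) and 24.07 (SD 4.35); two-sided alpha 0.05; power 0.9; dropout 30%. **Assumed:** baseline–week-6 correlation ρ of 0.3, 0.5 or 0.7.

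**1. Reproducing the plan's figure.** Difference in final means: 27.33 − 24.07 = 3.26. Pooled final SD: √[(4.15² + 4.35²)/2] = 4.25.

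- Noncentral t: 36.7 per arm, so 37 per arm, 74 in total.
- Normal approximation with the larger SD: 2 × (1.960 + 1.282)² × (4.35/3.26)² = 37.4, so 38 per arm, 76 in total.
- Dropout: 38/0.7 = 54.3, so 55 per arm, 110 in total.

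The plan's 76 and 110 therefore fit an unadjusted two-sided t-test on final scores. Its power at 38 per arm is 91%.

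**2. Power of the other candidates at 38 per arm.**

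- Change score: the difference in mean change is (27.53 − 24.07) − (27.40 − 27.33) = 3.46 − 0.07 = 3.39. The SD of change is √(s₀² + s₁² − 2ρs₀s₁), with s₀ = √[(4.91² + 4.61²)/2] = 4.76 and s₁ = 4.25.
- ANCOVA: difference 3.26, residual SD 4.25 × √(1 − ρ²).

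| | ρ = 0.3 | ρ = 0.5 | ρ = 0.7 |
|---|---|---|---|
| SD of change | 5.35 | 4.53 | 3.52 |
| Power, change-score t-test | 78% | 90% | 98.5% |
| N for 90% power, change score | 108 | 78 | 48 |
| ANCOVA residual SD | 4.06 | 3.68 | 3.04 |
| Power, ANCOVA | 93% | 97% | >99% |
| N for 90% power, ANCOVA | 68 | 56 | 40 |

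Mann–Whitney on normal data needs about 37/(3/π) = 38.7, so 39 per arm, 78 in total; its simulated power at 38 per arm is about 89–90%.

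**3. False-positive rate when more than one result could count.** Simulation with no treatment effect: 38 per arm, normal scores rounded to whole points, regression on arm, baseline Y-BOCS, sex and a depression score, the last two unrelated to outcome; 40,000 trials per correlation. Each test alone rejected in about 5%.

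| Success if any of these has p < 0.05 | ρ = 0.3 | ρ = 0.5 | ρ = 0.7 |
|---|---|---|---|
| t-test or regression | 6.7% | 7.4% | 8.3% |
| Final-score or change-score t-test | 8.9% | 9.2% | 9.5% |
| All four, including Mann–Whitney | 10.4% | 10.9% | 11.4% |

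Separate runs of 10,000 trials gave 6.3 / 7.4 / 8.2% for the first row and 10.1 / 11.2 / 11.6% for the last.

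**The case against.** The strongest reply is that the plan does define its test. Section 2.10 names a two-sided t-test at 6 weeks and gives it alpha, power and N. That stands. A reader might infer that the 5% and 90% belong to no defined test; the text does not support this, and the N reproduces for the test named.

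Second, a reader might infer that three tests are all run on the primary endpoint. The wording does not support that either. In section 2.11 the t-test and Mann–Whitney are joined by the word respectively, and the sentence on the disability and depression scales in the same section says that Mann–Whitney applies when normality fails. They are alternatives. An error rate that counts both is therefore an upper reading, and so is one that adds the change-score test, which comes from the abstract and is not listed in 2.11.

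Third, one might argue that the Kolmogorov–Smirnov check has almost no power to detect non-normality. That depends on whether the p-value is corrected for the estimated mean and SD. The text does not say, and a QQ-plot is named beside it, so the argument is not made here. Nor does the gate by itself visibly inflate error: with normal data, a simulation of the gated test alone gave 5.4 / 5.0 / 5.6%.

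Fourth, an unadjusted test is valid in a randomised trial, and much detail may properly sit in an SAP that is not shown. Both are true. But the article itself states the endpoint and the tests, and no SAP could follow all four places without overriding one of them.

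**Conclusion.** The point holds in this form: one test is powered, but it is not kept as the single deciding analysis, and the endpoint is worded as a reduction in one place and as a score without a time point in another. The unresolved matters are the role of the regression, the switching rule, and change versus score.

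On the narrow reading, with the t-test or the regression able to count, the error is about 7–8% instead of 5%; about 10–11% is the ceiling if every candidate could count. The power loss is conditional. If the abstract's change score governs, power at 38 per arm falls to 78% at correlation 0.3, is about 90% at 0.5 and exceeds 90% at 0.7. ANCOVA meets the target throughout. Everything except the 91% for the final-score t-test and the normal-data figures for Mann–Whitney depends on the assumed correlation.

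Because it concerns the primary test, this should be settled before the trial starts.

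**What to change.** Use the same statement in the abstract, 2.8.1, 2.10 and 2.11. The primary analysis is Y-BOCS total at week 6, intention-to-treat, by ANCOVA with arm, baseline Y-BOCS, sex, baseline HDRS and site, two-sided 0.05, pooled over the multiple imputations of section 2.12. Site is the stratification factor in 2.2.1; small sites can be pooled or site fitted as a random effect. With baseline Y-BOCS in the model, the estimated treatment effect is the same for final score and for change, so the endpoint conflict disappears.

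Drop the normality gate for the primary test. Label the unadjusted t-test and the Mann–Whitney test as sensitivity analyses. Keep N = 110, and state in 2.10 that the 0.9 power refers to the unadjusted final-score t-test and is expected to be conservative for ANCOVA.

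The cost is wording only: sex, depression and baseline severity are already named as covariates, site is already known, and no additional patients or data are needed. The Limitations section says that the trial has not been implemented, so nothing already done has to be revised.
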